### 13.4.2 Ethical and regulatory requirements

Research Ethics approval for this sub-study will be sought from the NRES Committee North West – Greater Manchester East by way of major amendment to the previously approved protocol (ref. 14/NW/0035). Permission to conduct the sub-study will be sought from the R&D department at participating centres.

Patients will be recruited onto the study using the standard REQUITE patient information sheet and consent forms and as per consent procedure outlined in the main study. The withdrawal criteria and procedure from the main REQUITE study shall apply.

### 13.4.3 Management and oversight arrangements

This sub-study will be overseen by the main REQUITE Study Management Group (SMG), as the majority of patients in this sub-study will come from the main study. Study data will be overseen by the REQUITE data manager. The conduct of this sub-study will be monitored as part of the arrangements for the main study.

The University of Manchester will remain as sponsor for this sub-study. The contact point is:

[name]

Associate Vice-President (Research Integrity)

The University of Manchester

[name]

Email: [[contact]](mailto:[contact])

[contact]

The University of Manchester has insurance for research involving human subjects that provides cover for legal liabilities arising from its actions or those of its staff, subject to policy terms and conditions. For participating sites which are part of the NHS, the NHS indemnity scheme will also apply.

### 13.4.4 Sub-study publication

For the main publication(s) arising from this sub-study, it is anticipated that all contributors will be authors with the proviso that clinicians contributing patients must have contributed 20 patients or more. This includes all centres where breast cancer patients have been recruited.

A formal publications policy is due to be generated by the REQUITE SMG, which all participants will be asked to sign up to. All presentations and publications relating to the sub-study will require authorisation by the Steering Committee.

The main results of the REQUITE-AB sub-study will be published in a peer-reviewed journal, on behalf of all collaborators. The manuscript will be prepared by a writing group, appointed from participating centres and the REQUITE Steering Committee.

# 14.0 SUB-STUDY 2: REQUITE-AB-QOL

## 14.1 Summary

| **TITLE** | REQUITE Acute Breast Qualitative Interview Study (REQUITE-AB-QOL) |
| --- | --- |
| **STUDY DESIGN** | Qualitative study embedded within the REQUITE main study conducting semi-structured interviews with a purposive sample of breast cancer patients recruited into the main study |
| **TARGET DISEASE** | Cancer of the breast |
| **PRIMARY STUDY OBJECTIVE** | To explore participants’ attitudes to and beliefs about a predictive tool for acute radiotherapy side-effects and any impact on participants’ decision-making |
| **SECONDARY STUDY OBJECTIVE** | To explore participants’ experience of breast radiotherapy. |
| **PARTICIPATING SITES** | University of Leicester |
| **STUDY POPULATION** | Breast cancer patients recruited into the main REQUITE or REQUITE-AB sub-study |
| **RECRUITMENT TARGET** | Sample size to be determined by qualitative data generated from participants, but it is anticipated that no more than 25 to 30 patients will be interviewed. |
| **FOLLOW UP VISITS** | Single interview to take place on or shortly after completion of radiotherapy. |
| **STUDY DURATION** | Patients to be recruited over the course of the 24-month recruitment period of the main REQUITE study |
| **SAMPLE COLLECTION** | Single semi-structured interview, digitally recorded and transcribed |
| **POWER CALCULATIONS** | Given the qualitative methodology, there is no power calculation. |

## 14.2 Background

### 14.2.1 Radiotherapy impact on quality of life (QoL)

A relative lack of evidence about the effects of breast cancer treatments on QoL can impair doctor-patient communication and limit the patient’s understanding of their treatment. Breast cancer patients face difficult treatment decisions and should be guided by meaningful information about expected QoL and radiation toxicity outcomes.

The main REQUITE study and the REQUITE-AB sub-study seek to collect QoL endpoints using validated patient-reported outcome measure (PROM) instruments in addition to genotyping data and clinical end-points. If clinicians are to inform patients more accurately about the risks and impact of side-effects, this will require accurate prediction tools incorporating PROM endpoints. However, the acceptability of any such tool to breast cancer patients should also be evaluated.

More than half of all women due to undergo breast cancer radiotherapy are anxious about side-effects and changes to the appearance of their breast.^[[51]](#footnote-51)^ With a focus on acute side-effects, recent qualitative research has illustrated a predominantly negative perception of radiotherapy.^[[52]](#footnote-52)^ The same authors also published a thematic analysis of semi-structured interviews with 20 women immediately after breast radiotherapy.^[[53]](#footnote-53)^

### 14.2.2 Rationale for the study

Based on their experience of breast radiotherapy, patients’ views on a predictive tool for acute radiotherapy side-effects should be explored, to determine how any such test should be implemented in clinical practice and how it would impact on patients’ decision-making. Research is needed to ensure that any such decision-making tool is acceptable to for breast cancer patients.

## 14.3 Sub-study research plan

### 14.3.1 Study objectives and design

The main objective of the REQUITE-AB-QOL study is to explore patients’ attitudes to and beliefs about a predictive tool for acute radiotherapy side-effects and the impact on patients’ decision-making around different breast cancer treatments.

Embedded within the main cohort study, qualitative data will be collected through semi-structured interviews with a sample of patients on completion of radiotherapy at participating centres. This will serve to explore patients’ attitudes and beliefs about a future predictive test for radiotherapy side-effects or treatment decision-making tool and to assess the acceptability of such a tool.

### 14.3.2 Patient selection and recruitment

A purposive sample of breast cancer patients recruited into the main REQUITE study or the REQUITE-AB sub-study at the participating centre will be interviewed. Eligible patients will be approached if they would be willing to participate in an audio-recorded in-depth interview. There is no set number of participants to be recruited, given the iterative nature of this part of the research. Sample size will be determined by data generated from participants until no new topics emerge and thematic saturation is reached.^[[54]](#footnote-54)^ However, it is anticipated that no more than 25 to 30 patients will be interviewed. It is expected that the sample will include adequate representation of age, ethnicity, different breast sizes, types of breast surgery, co-morbidities (e.g. diabetes or anxiety/depression) and degrees of skin toxicity.

Patients will be consented for the interviews using an additional consent form and additional patient information sheet.

### 14.3.3 Study methodology and data analysis

Each patient interview will take place on or shortly after completion of radiotherapy, anticipating that most patients will have experienced acute skin toxicity by then. Patients will be offered a choice of location – either a private room at the hospital away from the clinical areas or to be interviewed in their own home. If patients are interviewed at home, then a check-in/check-out procedure will be followed by the interviewer with the hosting University department and the interviewer must remain contactable by mobile phone. Interviews will last approximately an hour, but no more than one and a half hours. Each interview will be recorded on a digital Dictaphone and transcribed verbatim and fully anonymised, using professional transcription services.

As some of the issues explored in this part of the project will be personally sensitive, individual interviews will be conducted rather than focus groups. While following an interview guide, this approach also allows participants to be probed further to get a rich picture of their experience. The researcher conducting interviews will not be involved in the patient’s usual medical care, but may be medically trained. At the beginning of the interview, it will be explained to patients that the interviewer will not be able to answer questions concerning their own treatment, but will have knowledge and training to direct any patient queries to the correct healthcare professional. Patients’ responses will be completely anonymised for the data analysis.

At the start of the interview, patients will be asked to talk about their experience of breast radiotherapy without interruption by the interviewer. This will serve to ease the participant into the interview and to build up a rich background picture of their treatment experience. The idea of a predictive test for acute radiotherapy side-effects and reasoning behind this will then be introduced by the interviewer. Participants will also be shown different fictional case vignettes with reports; one suggesting risk of severe toxicity, one suggesting mild or no toxicity only, and one inconclusive test result. Patients will be reassured that severe toxicity is relatively uncommon. After engaging with this information, the patient will be invited to describe their thoughts and feelings.

Following the initial response, the interview guide will include probes in areas of further inquiry relating to the treatment experience and the feasibility and implementation of any predictive test – in particular, acceptability, demand, and practicality, as well as integration into the treatment decision-making process.^[[55]](#footnote-55)^ For example, participants will be asked, if they thought if a predictive test would have been appropriate for them, how interested they would be in getting a report, and at what level of risk the result would influence their treatment decision and options for alternative treatment. To ensure that important themes have not been missed, the interview will be concluded with the question: ‘Is there anything else you would like to tell me?’

Emerging themes will be identified through systematic coding of the transcripts, using Nvivo software or similar. Transcripts will be analysed independently by the researcher and checked with a co-researcher every three to five interviews to ensure reliability of the data coding. Thematic analysis will take place in parallel to data collection through familiarization with the data and constant comparison of transcripts to inform further data collection until thematic saturation is achieved.

Thematic codes will subsequently be sorted into broader themes. On completion of the interviews, coding and themes will be finalised by the research team, following published RATS guidelines for qualitative research.^[[56]](#footnote-56)^

Thematic analysis is a particular type of qualitative analysis focused on recognising, analysing, and reporting repeating themes across a data set.^[[57]](#footnote-57)^ It is not tied to a specific theory or epistemology, therefore one has to be explicit why this method is used. First, thematic analysis in this study will be driven by an interest in understanding whether a test for acute radiotoxicity would be acceptable to breast cancer patients. Secondly, although this approach may lose some of the depth of a more abstract analysis, the aim is to generate a thematic description of the patients’ feelings, attitudes and concerns about any such test. Themes identified in relation to the treatment experience may also be used to qualify individual scores from the PROM questionnaires obtained as part of the REQUITE study.

## 14.4 Sub-study research arrangements

### 14.4.1 Compliance and data protection

All investigators and researchers involved with the study must comply with the national requirements for data protection with regard to the collection, storage, processing and disclosure of personal information and agree to uphold the appropriate core principles.

Patient notes and study files at site must be kept in a secure storage area with limited access. Interviews will be audio-recorded and then transcribed in anonymized form and stored on password-protected university computers. Anonymized data will be emailed in encrypted format or uploaded via secure servers

Any access required to the REQUITE database will be strictly limited via usernames and passwords. Published results will not contain any personal data that could allow identification of individual patients.

### 14.4.2 Ethical and regulatory requirements

The study will be conducted in accordance with the approved protocol, the Declaration of Helsinki, ICH Guidelines for Good Clinical Practice (ICH GCP), relevant regulations and standard operating procedures.

Research Ethics approval for this sub-study will be sought from the NRES Committee North West – Greater Manchester East by way of major amendment to the previously approved protocol (ref. 14/NW/0035). Permission to conduct the sub-study will be sought from the R&D department at participating centres.

The local Principal Investigator (PI) must ensure that the study protocol, patient information sheet, consent form, family doctor letter and submitted supporting documents have been approved by the appropriate regulatory bodies and research ethics committee(s) prior to any patient recruitment.

Any agreed substantial amendments must also be submitted and receive ethical and regulatory approval prior to implementation. It is the responsibility of the PI at each site to ensure that the study has all the necessary approvals in place. A site initiation meeting must be completed prior to each study centre opening to recruitment.

Patients will be recruited onto the sub-study using a separate REQUITE-AB-QOL patient information sheet and separate consent form. A patient information sheet will be presented to potential participants detailing the nature of the study, the implications of participating and any potential risks or inconveniences involved in taking part. It will be clearly stated that the participant is free to withdraw from the study at any time, for any reason, without prejudice to future care and with no obligation to give the reason for withdrawal. The participant will be allowed sufficient time (a minimum of 24 hours) to consider the information and decide whether to take part before consent is sought. Written informed consent will then be obtained by means of patient dated signature and dated signature of the person who presented and obtained the informed consent.

Patients wishing to withdraw from the study will not be replaced. If a participant decides to withdraw, their coded blood samples and information will be retained for use within REQUITE and for future medical research unless the patient makes a specific request otherwise. If specifically requested (either verbally or in writing to a member of the research team), the blood samples will be destroyed and the medical information removed from the REQUITE database.

### 14.4.3 Management and oversight arrangements

This sub-study will be overseen by the main REQUITE Study Management Group (SMG), as the patients in this sub-study will come from the main study or REQUITE-AB sub-study. The conduct of this sub-study will be monitored as part of the arrangements for the main study.

The University of Manchester will remain as sponsor for this sub-study. The contact point is:

[name]

Associate Vice-President (Research Integrity)

The University of Manchester

[name]

Email: [[contact]](mailto:[contact])

[contact]

The University of Manchester has insurance for research involving human subjects that provides cover for legal liabilities arising from its actions or those of its staff, subject to policy terms and conditions. For participating sites which are part of the NHS, the NHS indemnity scheme will also apply.

### 14.4.4 Sub-study publication

For the main publication(s) arising from this sub-study, it is anticipated that all contributors will be authors. The main results of the REQUITE-AB-QOL sub-study will be published in a peer-reviewed journal. The manuscript will be prepared by a writing group, consisting of researchers and investigators, and, where appropriate, REQUITE SMG members of participating centres as per publications policy.

A formal publications policy due to be generated by the REQUITE SMG, which all participants will be asked to sign up to. All presentations and publications relating to the sub-study will require authorisation by the SMG.

# 15.0 SUB-STUDY 3: REQUITE–CHRONO

## 15.1 Summary

| **TITLE** | REQUITE-CHRONO: Circadian rhythm REQUITE sub-study |
| --- | --- |
| **STUDY DESIGN** | Questionnaire study gaining further information from REQUITE breast and prostate cancer patients recruited into the main study |
| **TARGET DISEASE** | Cancer of the breast and prostate |
| **PRIMARY STUDY OBJECTIVE** | To establish if there is a link between chronotype (morning-evening preference) and radiotherapy toxicity. |
| **SECONDARY STUDY OBJECTIVE** | To establish if there is a link with chronotype and circadian rhythm genes. |
| **PARTICIPATING SITE** | University of Leicester |
| **STUDY POPULATION** | Breast and prostate cancer patients recruited into the main REQUITE study |
| **RECRUITMENT TARGET** | 350 breast and 250 prostate patients will be sent the questionnaires. 50% return rate is expected. |
| **FOLLOW UP VISITS** | No |
| **STUDY DURATION** | Patients to be recruited over the duration of the main REQUITE study |
| **SAMPLE COLLECTION** | Munich Chronotype Questionnaire |
| **POWER CALCULATIONS** | In our small pilot study we observed a significant protective effect if evening chronotype patients were treated in the afternoon. In total, in this pilot study, 28% of patients received their radiotherapy in the afternoon. None of the patients with evening chronotype experienced late toxicity however 47% of patients in the normal or early chronotype group did. Assuming 50% response rate (n=300) then the study would be powered to 98.0% using the same expected values as the pilot study. |

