**Genotyping**

It is estimated that 2-year toxicity data (1-year for lung) will be available for 75% of enrolled patients. Based on effect sizes observed for genetic associations with radiation toxicity, a power calculation for the genetic assays shows that 1,575 patients for breast and prostate cancer each has 80% power to detect a RR of >1.56 for at least grade 2 toxicity (α = 5 x 10^-5^ for 1000 SNPs, allele freq = 0.25, toxicity rate = 20%), or with more stringent criteria a 90% power to detect a RR >1.66 (α = 1 x 10^-5^, allele freq = 0.25, toxicity rate = 20%). For 825 patients with lung cancer the detectable RR would be 1.78 and 1.92.

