### 15.3.2 Patient selection and recruitment

All breast and prostate cancer patients recruited to the main REQUITE study at the University of Leicester will be approached to take part in this sub-study. This will give a maximum sample size of 600. However, it is anticipated that there will be a 50% return rate giving 300 participants. It is expected that the sample will include adequate representation of age, ethnicity, disease factors, co-morbidities (e.g. diabetes or anxiety/depression) and degrees of toxicity.

Patients will be consented for the questionnaire sub-study using an additional consent form and additional patient information sheet.

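### REQUITE-CHRONO's 98.0% power is overstated: it counts every returned questionnaire as evaluable for late toxicity and takes a small pilot's 0% event rate as the true rate

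*Protocol*

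**What the plan says.** Protocol section 15.1 gives the recruitment basis as "350 breast and 250 prostate patients will be sent the questionnaires. 50% return rate is expected". Section 15.3.2 repeats it: "However, it is anticipated that there will be a 50% return rate giving 300 participants". Neither section makes any further allowance for loss.

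The effect size in section 15.1 comes from a pilot: "In our small pilot study we observed a significant protective effect if evening chronotype patients were treated in the afternoon". The same cell adds that "in this pilot study, 28% of patients received their radiotherapy in the afternoon" and that "None of the patients with evening chronotype experienced late toxicity however 47% of patients in the normal or early chronotype group did". It concludes: "Assuming 50% response rate (n=300) then the study would be powered to 98.0% using the same expected values as the pilot study".

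The primary objective in section 15.1 is "To establish if there is a link between chronotype (morning-evening preference) and radiotherapy toxicity", with no restriction by time of treatment.

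For the main study, section 7.1 (Genotyping) says: "It is estimated that 2-year toxicity data (1-year for lung) will be available for 75% of enrolled patients". The Study Summary (section 1.0) says the same. Both main-study power calculations in section 7.1 use a toxicity rate of 20%.

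**The concern.** Three features make the 98.0% look too favourable.

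- **Missing outcomes.** A returned questionnaire gives a chronotype, not a toxicity outcome. The outcome comes from main-study follow-up, where the protocol itself plans for 75% availability.
- **Zero taken as the truth.** A 0% rate observed in a small pilot is the most favourable value possible for the evening group. A replication calculated at that value has no margin for the pilot having been lucky.
- **Unclear contrast.** The pilot effect is described for evening types treated in the afternoon, while the objective concerns chronotype in general. The text does not say which of these the 98.0% refers to.

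Section 15.3.1 says the sub-study is meant to validate the pilot. A null result from a study believed to have 98% power would be read as refuting the pilot. If the real power is materially lower, that reading would be unsafe.

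**Working it through.** **Inputs from the Protocol.** 350 + 250 = 600 questionnaires; 50% returned = 300 (15.1, 15.3.2). Afternoon share 28%, so 0.28 × 300 = 84 (15.1). Pilot rates 0% and 47% (15.1). Availability 75% (7.1), so 0.75 × 300 = 225 and 0.75 × 84 = 63.

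**Not given, so assumed.** Two-sided alpha of 5%; the share of evening types; the test. Three methods are therefore shown: exact power of Fisher's test, exact power of the chi-square test, and the normal approximation

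power = Φ[(|p2 − p1| − 1.96·s0) / s1],

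with s0 = √[p̄(1 − p̄)(1/n1 + 1/n2)], s1 = √[p1(1 − p1)/n1 + p2(1 − p2)/n2] and p̄ the pooled rate.

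**Step 1: reproduce 98.0%.**
- Taking 28% as the group split (84 v 216) gives over 99.99%, so that is not the calculation.
- Taking the 84 afternoon patients with a 10% evening share (8.4 v 75.6): p̄ = 0.423, s0 = 0.1797, s1 = 0.0574; (0.47 − 1.96 × 0.1797)/0.0574 = 2.05, so power is 98.0%.
- Taking all 300, about 6 evening types (1.9%) would also give 98.0%, but that share seems too small to be the intended one.

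The second reading is the most plausible match. It rests on a share the Protocol does not state.

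**Step 2: apply 75% availability only.** With 6.3 v 56.7: s0 = 0.2075, s1 = 0.0663; (0.47 − 1.96 × 0.2075)/0.0663 = 0.96, so power is 83%. In whole patients (6 v 57) it is 63% by Fisher and 81% by chi-square. In the all-300 reading, the normal approximation falls to about 46%.

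**Step 3: relax the 0% as well.** Half the reference rate is 0.47/2 = 23.5%. With 6 v 57, power is 12.9% (Fisher), 16.1% (normal) and 17.7% (chi-square).

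**Step 4: vary what is unknown.** Power in %, whole patients:

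| Analysis set | Evening v other | Rates | Fisher | Chi-square | Normal |
|---|---|---|---|---|---|
| Afternoon, 84 | 8 v 76 | 0 v 47% | 98 | 99 | 97 |
| Afternoon, 63 | 6 v 57 | 0 v 47% | 63 | 81 | 79 |
| Afternoon, 63 | 9 v 54 | 0 v 47% | 98.5 | 99 | 97 |
| Afternoon, 63 | 6 v 57 | 23.5 v 47% | 13 | 18 | 16 |
| Afternoon, 63 | 19 v 44 | 23.5 v 47% | 35 | 43 | – |
| Afternoon, 63 | 19 v 44 | 0 v 20% | 53 | 68 | 59 |
| Afternoon, 63 | 25 v 38 | 0 v 20% | 66 | 80 | 71 |
| All, 225 | 22 v 203 | 0 v 20% | 86 | 97 | 86 |

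The 20% rows are sensitivity values borrowed from the main-study calculations.

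**Step 5: vary the availability.** If 90% of responders had toxicity data (an illustration, not a Protocol figure), both standard errors in Step 1 are divided by √0.9: (0.47 − 1.96 × 0.1894)/0.0605 = 1.63, so power is about 95%.

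**The case against.** The 98.0% is openly conditional on the pilot's values, and the pilot is called small. No slip of arithmetic is shown, since a reasonable set of inputs returns the figure. That stands: the fault lies in the inputs, not in the computation.

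The 75% describes enrolled patients. Those who return a questionnaire may be better followed up. That stands as a caution, and Step 5 shows its effect. But the Protocol offers no other figure, and assuming complete data is not supported anywhere.

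The loss from missing data is also sensitive to the unknown evening share. With 7 evening types of 63 the Fisher power is 85%, with 8 it is 96%, and with 9 or more it is back at about 96% or higher under the pilot rates. This stands, and it is why the result must be given as a range.

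A reader might infer that power is at most about 50% once the 75% and the main study's 20% toxicity rate are applied. The documents do not support that. Such a ceiling needs an afternoon-only analysis and an evening share of about 26% or less (normal approximation), and neither is stated. At 0% v 20%, 63 afternoon patients already give 53% to 68% with 19 evening types. All 225 patients give 86% or more at a share of about 10%. Nor is 20% a planning value for CHRONO: it belongs to the main-study genotyping and apoptosis calculations, the former for grade 2 or worse, while CHRONO does not define its late toxicity. A different rate under a different definition is no contradiction.

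Finally, the sentence giving 0% and 47% is not itself limited to afternoon patients, and section 15.2.2 reports a chronotype correlation without mentioning treatment time. The afternoon-only reading is therefore an inference, which is a further reason to have the contrast stated.

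**Conclusion.** The point holds. The 98.0% is overstated because it assumes complete toxicity data against the Protocol's own 75%, and because it takes a zero event rate from a small pilot as the truth. In the reconstruction that best matches the stated figure, the first correction alone leaves about 63% to 83%, depending on the test. Adding a halved rather than abolished risk leaves about 13% to 18%. These sizes rest on a two-sided 5% level, an afternoon-only contrast, an evening share near 10%, and 75% availability among responders. With a larger share or an all-patient analysis the loss is smaller, and under the unchanged pilot rates it can be negligible. No single replacement figure or upper limit can be derived.

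Separately, the contrast described for the power (evening types treated in the afternoon) does not clearly match the stated primary objective (chronotype and toxicity in all patients).

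**What to change.** In section 15.1, replace the 98.0% with the power for about 225 evaluable patients, of whom about 63 would be treated in the afternoon, for whichever contrast is to be the primary analysis. If better follow-up is expected among responders, state that figure and its basis.

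State the expected share of evening types, the alpha level and sidedness, the test, and the toxicity definition behind the 47%. Give a range of power rather than one value. It should include a non-zero toxicity rate in evening types and a lower reference rate; the main study's 20% would serve as a sensitivity value. Make the wording of the primary objective agree with the chosen contrast.

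The cost is a change of sub-study text and a less favourable stated power. No extra patients, visits or samples are needed.
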